## Abstract

**Background:**

The Bacillus Calmette-Guérin vaccine (BCG) against tuberculosis (TB) shows beneficial nonspecific effects, which are likely related to innate immune training. Until 2016, a single BCG dose was administered to all newborns in Portugal. In July 2016, a clinical guideline established that only children under 6 years belonging to high-risk groups should receive BCG. This might have prevented nonvaccinated children from developing trained immunological responses as effectively as BCG-vaccinated children.

**Objective:**

This study aims to investigate if there is variation in TB-related and all-cause mortality, and severe, moderate, or mild morbidity in children under 5 years of age, and whether such variation might be explained by the BCG vaccination policy change in 2016.

**Methods:**

This population-based historical birth cohort study includes children under 5 years of age born in Portugal between July 1, 2010, and June 30, 2021. Newborns with low birth weight, premature status, or known or suspected HIV infection are excluded. The follow-up period is until the completion of 5 years of age or the end of follow-up (June 30, 2021). The study will use secondary data from the National Health Service user registry, death certificate database, vaccination registry, communicable diseases surveillance system, TB surveillance system, diagnosis-related group information system for hospital admissions and emergency department visits, and primary health care information system. The data will be linked. Primary outcomes include person-time incidence rates of death (all causes and TB), TB diagnosis, and all causes and some specific causes of severe, moderate, or mild morbidity, and the incidence rate ratio of nonvaccinated to BCG-vaccinated children. We will compare the probability of surviving the first and fifth years of life or of not having severe, moderate, or mild morbidity during the follow-up period according to exposure (BCG vaccinated or nonvaccinated, number of doses, and time from birth until the first dose), using the log-rank test for assessing differences in survival rates between exposed and nonexposed children and hazard ratios for quantifying the differences. Moreover, we will perform a proportional hazards regression analysis.

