### BCG Vaccination in Portugal

In Portugal, BCG began to be routinely administered to all newborn children in 1965. Until 2016, a single BCG dose was administered to all newborns, typically before discharge from the maternity ward (most births in Portugal are hospital-based) or as early as possible thereafter [20].

In June 2016, a clinical guideline established that only children under 6 years of age who belong to high-risk groups (those originating from countries with high TB incidence; having contact with active cases or persons under prophylaxis; having HIV-positive mothers; having parents with a alcohol or drug abuse problem and antecedents of TB; having parents who have been in prison in the last 5 years; living in high-risk TB communities; or traveling to high-incidence countries) should be vaccinated as close to birth as possible [21]. Some of these risks were not considered individually but by proxy, with some parishes (freguesias) thus considered high risk for the criteria defined.

In 2016, 42% of children under 1 year of age had received BCG (compared to 98% in the previous year) [20]. Between 2016 and 2018, the incidence of TB increased by 16% in children under 1 year of age (from 7.0 to 8.1 per 100,000 inhabitants) and 192% in children aged 1 to 5 years (from 2.6 to 7.6 per 100,000 inhabitants) [20].

Between the adoption of the high-risk strategy for BCG vaccination in 2016 and 2018, the infant mortality rate (IMR) remained stable at 3.2‰ to 3.3‰, with important variations between the considered years [20]. In 2019, there was a decrease to 2.8‰. The mortality rate in children under 5 years of age decreased from 3.4‰ in 2016 to 3.0‰ in 2019, but not constantly in this period (eg, during 2018 it was 3.5‰) [20]. No death in children under 5 years of age has been attributable to TB since the implementation of the high-risk strategy for BCG [20]. Nevertheless, the number of severe cases of TB in children under 5 years of age decreased in 2020 compared to 2018 (4 cases) and 2019 (7 cases), with just 1 case registered in a child without BCG vaccination [22].

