### Participants

The study will include children under 5 years of age born and registered in Portugal between July 1, 2010, and June 30, 2021. We have chosen this period because it will allow us to (1) compare the cohorts before and after the change in the BCG immunization strategy (Figure 1); (2) characterize children not vaccinated with BCG and their health outcomes (when universal BCG at birth was recommended); and (3) compare children exposed and not exposed to BCG after the 2016 change in the BCG vaccination strategy.

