### Measurements

Exposure is defined as having received the BCG vaccine during the first year of life and is measured using the vaccination registry. Variables include BCG (yes or no, and number of doses) and time from birth to BCG (in days).

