After obtaining the final database, we will compute person-time incidence rates for primary outcomes in BCG-vaccinated and nonvaccinated children. Using the Kaplan-Meier method, we will compute and compare the probability of surviving the first and fifth years of life or of not having a hospitalization, emergency department visit, or mild morbidity episode during the follow-up period according to exposure. Additionally, we will use a log-rank test for assessing differences in survival rates between exposed and nonexposed children and hazard ratios (and corresponding CIs) for quantifying the differences. To explore the effects of several variables on the survival outcomes, we will use proportional hazards regression analysis. If missing data are below 5%, we will use complete case analysis. Otherwise, the frequency and patterns of missing data will be analyzed, and if appropriate, we will use multiple imputation techniques.

Confounders to be measured and controlled for are sex, health unit, completeness and timeliness of vaccination status and scheme, socioeconomic status, and BCG strain (over the years, administered BCG has been provided by different producers, with different strains).

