## Results

This project was approved as an exploratory project by the Portuguese Foundation for Science and Technology in the 2021 competitive call for R&D projects (reference: EXPL/SAU-EPI/0067/2021). It was granted approximately €50,000 (US$ 53,869) and was started in January 2022.

During the first month of the project’s implementation, administrative and financial activities were carried out, with a summary of the project sent to members of the Scientific Advisory Board, including the planned activities.

In March 2022, database owners were contacted to present the project and discuss how to officially request the data. A document detailing all the data needed to carry out the study was prepared and sent to the Directorate General of Health. After approval from this body, Serviços Partilhados do Ministério da Saúde (SPMS) and Administração Central do Sistema de Saúde (ACSS) also had to provide authorization to access the data, with the last authorization given in October 2023.

We were informed that a UI would be provided for each database, based on the NHS user number, from the RNU, thus allowing direct linkage of records. However, some of the requested variables had to be reviewed and replaced given the Data Protection Law. In July 2023, a process of redefinition of the variables per database was initiated, with some of the variables requested not being supplied owing to legal restrictions (eg, date of birth had to be replaced by days from birth until the event and information if the child had been born before or after 2016) (Multimedia Appendix 1).

Data were received during October and November 2023. By mid-December, data from SINAVE had not yet been provided. No data were obtained from Svig-TB as we were not granted access. Some of the variables requested from this database were replaced by equivalent or proxy variables from SINAVE (Multimedia Appendix 1).

In November 2023, work was conducted in the databases already provided to restructure the databases, perform quality checks and cleaning, compute exposure variables, transform string variables into numeric variables, and perform coding.

By April 2024, we expect to start analyzing the full data set, which is expected to include around 970,000 children.

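### The comparison by time from birth to first BCG dose is not tied to one policy era, and the stated adjustment set has no birth period or TB-risk indication

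*Protocol article*

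**What the plan says.** - The Abstract (Methods) compares the probability of surviving, or of staying free of morbidity, "according to exposure (BCG vaccinated or nonvaccinated, number of doses, and time from birth until the first dose"). Statistical Methods repeats the Kaplan-Meier, log-rank and hazard ratio plan by exposure. Neither place limits the timing comparison to an era.
- The cohort is "children under 5 years of age born and registered in Portugal between July 1, 2010, and June 30, 2021" (Participants), so it spans the 2016 change.
- Under Measurements, "Exposure is defined as having received the BCG vaccine during the first year of life", and the timing variable is "time from birth to BCG (in days"). A late dose therefore means late within the first year.
- Under BCG Vaccination in Portugal, the universal-era dose was given "typically before discharge from the maternity ward". After the change only high-risk groups were eligible, and one listed ground is "having contact with active cases or persons under prophylaxis".
- The adjustment set in Statistical Methods is definite: "Confounders to be measured and controlled for are sex, health unit, completeness and timeliness of vaccination status and scheme, socioeconomic status, and BCG strain".
- Results reports that date of birth was withheld. The data carry days from birth to event and "information if the child had been born before or after 2016".
- Every primary row of Table 1 compares exposed with nonexposed children. None compares early with late doses.

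**The concern.** A comparison of early with late doses is fair only if the reason for being early or late is unrelated to the outcome, or is adjusted for. That reason changed in mid-2016. Before, coverage was about 98% and the dose was routine after birth. After, a dose marks a child as high-risk, and contact with a case or planned travel can arise weeks or months after birth. If the late fraction differs by era, and the outcome rate among vaccinated children also differs by era, an analysis of all births together turns the era difference into a timing difference.

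The Background cites evidence that earlier administration has greater effects. If post-change vaccinated children are sicker, era confounding would look like confirmation of that. If rates fell over time, it would mask or reverse a real effect. This is separate from the need to survive to the dose and from the newborn's condition: correct risk time and adjustment for birth weight would not remove it.

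**Working it through.** The article gives no figure for dose timing, so there is none to reproduce. The check asks how much bias an analysis without an era term could carry.

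**Inputs from the article.** About 970,000 children (Results); 11 birth years; coverage 98.2%-98.4% in 2010-2015 and 41.6% in 2016 (Table 1 footnote).

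**Assumptions, because the article is silent.** Even births; the split at July 2016; 98.2% coverage in the six years before; average coverage c of 5%-41.6% in the five years after; late share of first-year doses 2%-10% before and 5%-60% after; no true timing effect; post/pre rate ratio R among vaccinated children of 1.3, with 0.88 to show the opposite direction. The 0.88 is 3.0/3.4, the under-5 mortality change from 2016 to 2019. It covers all children and is not a before/after ratio, so it is only an illustration.

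**Step 1: who is vaccinated.** Births per year = 970,000/11 = 88,182. Vaccinated before = 88,182 × 6 × 0.982 = 519,567. Vaccinated after = 88,182 × 5 × c:

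| c | Vaccinated after | Share of all vaccinated born before the change | Ratio before/after |
|---|---|---|---|
| 5% | 22,045 | 96% | 23.6 |
| 20% | 88,182 | 85% | 5.9 |
| 41.6% | 183,418 | 74% | 2.8 |

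The last column is also the factor by which the late share after must exceed the late share before if post-change children are to be the majority of late doses.

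**Step 2: composition and false ratio.** Let s and e be the post-change shares of the late and early groups. The false late/early ratio is (1 − s + sR)/(1 − e + eR).

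Example with c = 20%, 5% late before and 30% late after:
- Late: 0.05 × 519,567 = 25,978 before and 0.30 × 88,182 = 26,455 after, so s = 26,455/52,433 = 0.505.
- Early: 493,589 before and 61,727 after, so e = 61,727/555,316 = 0.111.
- At R = 1.3: (1 + 0.3 × 0.505)/(1 + 0.3 × 0.111) = 1.11.

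| c | Late before / after | s | e | R = 1.3 | R = 0.88 |
|---|---|---|---|---|---|
| 20% | 5% / 5% | 0.15 | 0.15 | 1.00 | 1.00 |
| 20% | 5% / 10% | 0.25 | 0.14 | 1.03 | 0.99 |
| 20% | 5% / 30% | 0.51 | 0.11 | 1.11 | 0.95 |
| 41.6% | 2% / 60% | 0.91 | 0.13 | 1.23 | 0.90 |
| 41.6% | 10% / 5% | 0.15 | 0.27 | 0.97 | 1.02 |

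Over the grid with c from 10% to 41.6%, the false ratio at R = 1.3 runs from 0.97 to 1.23. It is 1.00 when the late share is the same in both eras. In the second row post-change children are only a quarter of late doses, yet some bias remains.

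**Step 3: within era.** Each stratum contains one era, so the between-era part of the ratio is 1.00 whatever the late shares.

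**Step 4: the 2016 births.** Half a year at 98.2% is 0.5 × 0.982 = 0.491 birth-years of vaccinated children, already more than the 0.416 that 41.6% coverage gives for the whole of 2016. The 2016 vaccinees could therefore all be universal-era newborns. Using 0.416 in place of 0.491 lowers the before-change total from 5.892 to 5.817 birth-years, about 1%, so Step 1 barely moves. It matters more for the remedy. If the supplied indicator places 2016 births in the later stratum, they make up 0.416/(0.416 + 4.5c) of its vaccinees: 0.416/0.641 = 65% at c = 5%, and 0.416/2.288 = 18% at c = 41.6%.

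**The case against.** The strongest reply is that the article never says the timing comparison combines the eras. Every primary row of Table 1 takes its exposed children from one era. Exposed children of the two eras meet only in the strain rows, where they are compared and not merged. Participants names within-era comparison as a purpose of the design, and the log-rank test is described as exposed against nonexposed. An article may also leave such detail to a fuller document.

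Part of this stands. A reader might infer that the plan pools births across 2016. That is the natural reading of one cohort with no restriction, but it is not stated. The reply does not remove the point, because the era discipline of Table 1 is not extended to timing and the adjustment set is stated as a definite list.

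A reader might also infer that late doses come largely from post-2016 high-risk children. The article does not support that. It asks for vaccination promptly after birth in both eras, defines risk partly by parish so that many later children would be offered BCG from birth, counts only first-year doses, and gives no distribution of age at dose. Universal-era vaccinees outnumber later ones by about 2.8 to 24 times under the assumptions above.

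Health unit, socioeconomic status and strain are in the list and partly stand in for geographic risk and period. They are not birth period or individual indication.

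**Conclusion.** The point holds as a gap in the stated analysis. The timing contrast has no era restriction and no Table 1 row, and its adjustment set lacks birth period and TB-risk indication. Late doses may be enriched for post-change high-risk children. They need not be the majority for bias to arise; it is enough that both the late share and the outcome rate differ by era.

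Size and direction are unknown. The range of 0.97 to 1.23 rests on assumed coverage after 2016, assumed late shares and R = 1.3, and ignores any partial correction from strain and health unit. It would be too strong to conclude that the timing result cannot be interpreted: with similar late shares in both eras the bias vanishes. The change is advisable because it is cheap and because one direction of bias mimics the expected finding.

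**What to change.** State in the analysis plan that:

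- The effect of time to first dose is estimated within era, using the before/after-2016 indicator already supplied.
- Births before 2016, all under universal BCG, form the main timing contrast.
- Later births are reported separately as secondary, with two caveats: 2016 births span the July 2016 change, and confounding by indication remains in that stratum. The plan should say on which side of the indicator the 2016 births fall.
- The eras are not combined in one unstratified Kaplan-Meier, log-rank or hazard ratio analysis by timing.

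A Table 1 row for timing would make this explicit. The cost is a few sentences and one variable already in hand. The downside is fewer late doses per stratum and so wider intervals. Stratifying removes the between-era bias only.

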Further studies in children from Denmark and Greenland failed to show a decrease in hospitalization due to infectious diseases in vaccinated children [13,14]. On the contrary, a cohort study of children from 19 different countries revealed that BCG-vaccinated children under 5 years of age had a lower risk of suspected acute lower respiratory infection [15]. In Spain, hospitalization rates due to respiratory infection were lower in BCG-vaccinated children, with an attributable fraction of 32% for children under 1 year of age, and a similar finding was noted for sepsis, with an attributable fraction of 53% [16].

A systematic review concluded that BCG has a beneficial effect on mortality in children, with differential effects according to age (earlier administration of the vaccine is associated with greater effects) [5]. Nevertheless, there has been a call for more research on the nonspecific effects of BCG [5,17]. Currently, studies are seeking to further investigate the nonspecific effects of BCG [18] in terms of the effects on allergy and infection [7], severe morbidity, nonaccidental hospital admission, and all-cause consultation in children under 5 years of age [19].

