#### Exclusion Criteria

The study will exclude newborns who have a weight of <2 kg, are premature (<37 weeks of gestation), or are known or suspected to have HIV infection.

The follow-up period will be until the completion of 5 years of age or the end of follow-up (June 30, 2021) (Figure 2).

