### Statistical Methods

Through data linkage, we will create a single database that links data from the birth registry, SICO, vaccination registry, SINAVE, Svig-TB, BDMH, and PHC database (SClínico) to reconstruct chronological sequences of morbidity and mortality events from birth until the completion of 5 years of life or the end of follow-up (for the 2018 cohort onwards).

In each of the databases, we will identify the data needed and whether a unique identifier (UI) exists and can be provided with the data set. After having access to the requested data and in case a UI is provided (and common to all databases), we will combine information based on that UI.

In case a UI is not provided, we will link data from several data sets using a range of proxy identifiers (eg, date and place of birth, sex, and place of residence) to identify probable matches.

The type of data linkage method to be used will depend on the type and quality of the linkage variables available in the data sets. However, we anticipate having to use a combination of deterministic and probabilistic methods. Before applying linkage methods, we will clean and standardize the data, thus identifying and removing errors and inconsistencies. Given the expected size of the data sets, we will then select sets of block attributes (eg, sex, date of birth, and initials) and compare record pairs with the same matched attributes within blocks. Subsequently, record pairs will be compared for each linkage variable, and an agreement score will be computed. This score will be used to weigh the probability of a record pair belonging to the same child [26,27].

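### Comparing survival from birth by age at first BCG gives later-vaccinated children a guaranteed death-free interval, so the mortality result favours delayed vaccination even when timing has no effect

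*Protocol article*

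**What the plan says.** All places are in the protocol article.

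- **Abstract, Methods:** survival of the first and fifth years, and freedom from morbidity, are to be compared "according to exposure (BCG vaccinated or nonvaccinated, number of doses, and time from birth until the first dose".
- **Measurements:** "Exposure is defined as having received the BCG vaccine during the first year of life and is measured using the vaccination registry". The variables listed with it include "time from birth to BCG (in days".
- **Statistical Methods, linkage:** the linked file is to "reconstruct chronological sequences of morbidity and mortality events from birth until the completion of 5 years of life". The time origin is therefore birth.
- **Exclusion Criteria:** "The follow-up period will be until the completion of 5 years of age or the end of follow-up (June 30, 2021".
- **Statistical Methods, analysis:** Kaplan-Meier will be used to "compute and compare the probability of surviving the first and fifth years of life" according to exposure, followed by proportional hazards regression.
- **Background:** a systematic review is cited as showing that "earlier administration of the vaccine is associated with greater effects".

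The article mentions no landmark age, delayed entry or exposure that changes with time. The Limitations section does not raise the matter.

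**The concern.** The timing label is set by something that happens after follow-up has begun. A child can be placed in a day-60 group only by living to day 60, whereas a child dosed on day 2 is exposed to nearly all of the neonatal risk under its label. The death-free time that comes with the label therefore grows with the variable being compared.

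The resulting error runs against the effect the Background leads one to expect. If earlier BCG does protect better, the comparison as written would understate that and might show the opposite. The Discussion intends the results to inform BCG vaccination policy, so a mistaken reading of dose timing would matter.

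**Working it through.** The article states no figure on this point, so there is none to reproduce. The question is what ratio the comparison would show if timing had no effect.

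**Inputs**
- From the article: birth origin, fixed timing label, survival at 1 and 5 years; infant mortality 3.2 per 1000 (lower end of the 2016-2018 range) and under-5 mortality 3.4 per 1000 in 2016; a 25% mortality reduction in a cited earlier study, used only as an illustrative effect (HR 0.75).
- Assumed, because the article gives no age distribution of deaths or doses: an early dose on day 2; a late window of days 29-90; cumulative share of first-year deaths F(t) = (t/365)^a, with a chosen so that F(28) is 30%, 40% or 60%, or a = 1 (constant hazard, F(28) = 7.7%).

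**Formula.** With rare deaths, the first-year risk attached to a dose on day d is proportional to 1 - F(d), because deaths before d cannot occur under that label. The null late/early ratio is the mean of 1 - F(d) over days 29-90, divided by 1 - F(2). If the early dose truly has HR 0.75 and the late dose no effect, the true late/early ratio is 1/0.75 = 1.33, and the apparent ratio is the null ratio divided by 0.75.

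| F(28) | Late: mean of 1 - F | Early: 1 - F(2) | Apparent ratio, no effect (truth 1.00) | Apparent ratio, early HR 0.75 (truth 1.33) |
|---|---|---|---|---|
| 7.7% (constant hazard) | 0.837 | 0.995 | 0.84 | 1.12 |
| 30% | 0.578 | 0.913 | 0.63 | 0.84 |
| 40% | 0.482 | 0.844 | 0.57 | 0.76 |
| 60% | 0.308 | 0.645 | 0.48 | 0.64 |

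Under a constant hazard the true benefit is attenuated. Under the three front-loaded patterns its direction is reversed.

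**Second death model.** With deaths spread evenly over the year, the null ratio against a day-1 dose is (365 - d)/364. This gives 0.98 (day 7), 0.93 (day 28), 0.76 (day 90) and 0.51 (day 180). With a true early HR of 0.75, the ratio crosses 1 when 365 - d = 0.75 × 364 = 273, that is at day 92. If instead 50% of infant deaths fall by day 7 and 70% by day 28, the null ratio is 0.30/0.93 = 0.32 at day 28, and the HR-0.75 scenario is already reversed there (0.32/0.75 = 0.43). Overall infant mortality of 1.0, 2.8 or 3.2 per 1000 gives essentially the same ratios.

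**Five years.** On the article's figures, infant deaths are about 3.2/3.4 = 94% of under-5 deaths. The 40% pattern then gives (0.94 × 0.482 + 0.06)/(0.94 × 0.844 + 0.06) = 0.60 at five years against 0.57 at one. Longer follow-up dilutes the bias only slightly.

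**Does the remedy work?** In a simulation of 970,000 children (assumed: 80% dosed on days 0-7, 20% on days 28-365, uniform deaths, no effect), the from-birth rate ratio was 0.46. Counting only post-dose person-time, stratified by age, gave 1.01. With early HR 0.75 and no late effect the two were 0.66 and 1.39, against a truth of 1.33.

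**The case against.** **How firmly the timing comparison is planned.** Dose timing appears in one clause of the abstract and as a listed variable. The Statistical Methods section does not name it, and no cut-points are given. A full protocol or analysis plan may hold the detail. That is a fair limit on how much weight the contrast carries. But the article does positively state a comparison of survival by time to first dose, a fixed label and a birth origin, and following those statements produces the bias.

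**The log-rank test.** A reader might infer that a log-rank test by dose timing is planned. The text does not say so: "we will use a log-rank test for assessing differences in survival rates between exposed and nonexposed children and hazard ratios". The timing contrast comes from the survival comparison, not from that test.

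**Certainty of reversal.** A reader might conclude that the timing result will come out reversed. The article does not support that. The cohort is limited to normal newborns of at least 37 weeks and 2 kg, and the Limitations section expects deaths of very young children to be under-recorded. Both could reduce front-loading of recorded deaths. BCG was typically given before maternity discharge or soon after, so many doses may fall in the first days. These points affect size, not direction.

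**Morbidity.** A hospitalisation, emergency visit or primary care contact can precede the dose, so the guaranteed event-free interval applies to death only. For morbidity the fault is that pre-dose events and person-time are counted under a dose not yet given.

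**Birth era.** A reader might also infer that early versus late dosing is largely 2010-2015 versus later births. The article does not show this. In each primary row of Table 1 the exposed group comes from one era, early dosing is the stated policy in both eras, and no age-at-dose distribution is given.

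**Conclusion.** The point holds for mortality by age at first BCG. The direction follows from the design alone: a birth origin with a label fixed by a later event favours later doses. The size rests on assumptions. For days 29-90 against day 2 with no true effect, the apparent first-year ratio is about 0.84 under a constant hazard and 0.63 to 0.48 if 30% to 60% of first-year deaths fall by day 28. It is near 1 (0.98 for day 7 against day 1, uniform deaths) if nearly all doses come in the first days and deaths are not front-loaded. A true advantage of earlier vaccination would be attenuated; reversal needs front-loaded deaths or late doses. For morbidity, the claim is limited to misallocated pre-dose events and person-time. The plan should be changed before the timing comparison is run.

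**What to change.** Do not compare survival from birth by time to first dose. Define the timing windows in days beforehand, then use one of two analyses:

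- **Landmark.** Start follow-up at the end of the latest timing window being compared, among children alive at that age (and event-free, for first-event outcomes). The exposure definition admits doses throughout the first year, so for first-year outcomes the windows must close well before day 365; otherwise no follow-up remains.
- **Delayed entry.** Use age as the time scale, let each child enter on the day of vaccination, and fit timing category as the covariate. Groups are then compared only at ages when both are under observation.

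In either case, count only events and person-time after the dose, for morbidity as well as death. Keep the contrast within one birth era, as the primary rows of Table 1 already do for the exposed group.

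No new data appear to be needed: the Results section says events are supplied as days from birth, with an indicator of birth before or after 2016. The work is wording and programming. The downside is precision, since deaths before the landmark no longer inform the timing comparison.
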